## Abstract

**Background:**

Evidence is lacking concerning the effect of additional trunk rehabilitation on gait performance. Investigating gait performance by both clinical and biomechanical outcome measures might lead to new scientific insights into the importance of the trunk during gait rehabilitation in people suffering from stroke. This protocol was written according to the SPIRIT 2013 Statement.

**Methods and design:**

An assessor-blinded randomized controlled trial will be conducted in patients with impaired trunk control after stroke. A total of 60 patients will be randomly allocated to the control or the experimental group by means of sealed opaque envelopes. They will receive either 16 h of additional trunk exercises (experimental group) or cognitive exercises (controls) for 1 h a day, 4 days a week for 4 weeks. Patients will also receive 2 h of standard care consisting of physiotherapy and occupational therapy. Gait performance will be assessed clinically by the Tinetti Test and biomechanically by means of a full body gait analysis. In addition, the effect of the exercise protocol on the trunk itself and trunk activities of daily living will be assessed by the Trunk Impairment Scale and the Barthel Index.

**Discussion:**

Despite the evidence demonstrating the importance of trunk control after stroke, studies about the effects of trunk rehabilitation on gait performance are inconsistent. In the current study, a more sophisticated treatment protocol will be used to enlarge therapeutic improvements, the relationship between clinical and biomechanical measures of gait performance can be investigated, and the sustainability of the effects of trunk exercises over time will be examined. Since clinical improvements are of greater importance to patients and physiotherapists, clinical assessment scales will be used as primary outcome measures.

**Trial registration:**

ClinicalTrials.gov, ID: NCT02708888. Registered on 2 March 2016.

**Electronic supplementary material:**

The online version of this article (doi:10.1186/s13063-017-1989-1) contains supplementary material, which is available to authorized users.

## Background

Several studies have demonstrated that truncal function is impaired in patients suffering from stroke. Therefore, it is of utmost importance to no longer neglect truncal function during rehabilitation. Impairments in truncal function are characterized by a diminished sitting balance, decreased trunk coordination, reduced trunk control and lower trunk muscle strength, and altered trunk position sense [1–5]. Subsequently, patients displayed increased lateral movements, but decreased vertical movements compared to healthy controls [6]. Rehabilitation programs, such as core stability training, sitting and reaching training, which aim to reduce these impairments, seemed to improve clinical measures of static and dynamic sitting and standing balance after stroke [7–10].

However, more research is necessary regarding the effect of trunk rehabilitation on gait performance. Cabanas-Valdes et al. (2013) concluded that although trunk training exercises could be an effective rehabilitation strategy for improving trunk performance, further confirmation is necessary with respect to gait performance [11]. Since gait performance can be measured by means of clinical and biomechanical assessment it is of interest to incorporate both assessment methods. This is to make sure that every aspect of walking is assessed. Although biomechanical analysis gives a more in-depth understanding of the biomechanical improvements in gait performance, clinical improvements are of greater importance to patients and physiotherapists as they assess functional tasks and are easier to use in a clinical setting.

The trunk has long been defined as a so-called passenger unit since it was suggested that it is carried by the lower limbs instead of actively contributing to ambulation [12]. Yet, a more recent study suggested that the role of the passenger unit in pathological gait must be recognized in the decrease of gait efficiency in neurological patients [13]. The trunk is, in fact, one of the main contributors to the increased mechanical work of the passenger unit. However, as the trunk is one of the main contributors to decreased gait, it should no longer be defined as a passenger unit. Therefore, the effects of additional trunk exercises on the trunk itself during ambulation should be examined more thoroughly.

Consequently, this study aims to explore the effects of additional trunk exercises on gait performance, as measured clinically and biomechanically, in people suffering from stroke who have been submitted to a rehabilitation hospital.

### Objectives

The primary objective of this study is to examine the effect of an additional trunk exercise program on gait performance after stroke. Primarily, clinical assessment of gait performance is made by the Tinetti Test (TT) and its subscales; secondarily, biomechanical assessment by a full body gait analysis. Trunk performance will be assessed by means of the Trunk Impairment Scale (TIS) and the independency of a patient’s performance concerning activities of daily living (ADL) by the Barthel Index (BI). Patients suffering from stroke will be receiving either 16 h of additional trunk exercises or the same duration of cognitive exercises for a period of 4 weeks.

The second objective is to explore the sustainability of the effects of trunk exercises over time. It is important to know whether the treatment effects are sustainable over time or if continuous therapeutic input is necessary to maintain the level of functioning even after patients are discharged home.

## Methods and design

### Study design and setting

The design of this study is a 4-week, assessor-blinded randomized controlled trial with a 1-month follow-up at an established rehabilitation hospital. Participants will be randomly allocated to either the experimental or the control group by simple randomization executed by an independent researcher who is not involved in the assessment or treatment of the patients. After participants agree to participate in this study, the independent researcher will draw one of the 60 envelopes (30 for each group) and will assign the participants to the allocated group. Patients will be recruited from the stroke population of the rehabilitation hospital RevArte, located in Edegem (Antwerp, Belgium). This rehabilitation hospital is a 194-bed facility and is able to offer inpatient and outpatient rehabilitation for approximately 300 patients at the same time. All participants will receive 16 h of either trunk or cognitive exercises in addition to the multidisciplinary standard care stroke rehabilitation program provided by the rehabilitation staff.

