### Procedures

#### Recruitment and selection

The time schedule of enrollment, assessment, interventions, and follow-up according to the Standard Protocol Items: Recommendations for Interventional Trials (SPIRIT) guidelines can be found in Fig. 1. Patients are recruited and screened for eligibility in three consecutive steps. Firstly, the treating physiotherapists will be thoroughly briefed concerning the inclusion and exclusion criteria of the study since they will be providing the researchers with the information for possible inclusion. Next, study information will be given to potential participants by the main researcher. This comprises the objective and description of the study, the duration of the study, and its risks and benefits. If the patients are interested in the study, an appointment will be made to provide more detailed information and to answer possible questions. When the patient agrees to participate in the study, the informed consent will be signed before obtaining medical record admission to guarantee privacy. Lastly, after obtaining informed consent the patients will be screened by the primary investigator to assure inclusion by means of the TIS and the FAC. Information concerning stroke diagnosis, medical history, and stroke onset will be acquired from patient records.

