#### Allocation

A blinded investigator will allocate patients to the control or the experimental group by means of concealed envelopes which will be kept off site.

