#### Blinding

Although we will try to blind patients, therapists, and assessors it is unlikely that patients and therapists will stay blind during the course of this study due to the nature of the applied treatment. However, to make sure that the risk of bias stays low, patients will be registered in the database by means of a patient ID code so assessors are blinded during analysis. Only the primary investigator will have knowledge regarding allocation.

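### Allocation concealment is not secured as written: the final eligibility screener is the one person said to know allocation, the draw is tied to agreement, and the fixed 30/30 envelope pool is misnamed simple randomization

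*Protocol article*

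**What the plan says.** All of this is in the protocol article.

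- **Method and person (Study design and setting).** Participants are allocated "by simple randomization executed by an independent researcher who is not involved in the assessment or treatment of the patients".
- **Pool and timing (same section).** "After participants agree to participate in this study, the independent researcher will draw one of the 60 envelopes (30 for each group"). The draw is tied to agreement. Confirmed eligibility is not mentioned.
- **Final eligibility check (Recruitment and selection).** "after obtaining informed consent the patients will be screened by the primary investigator to assure inclusion by means of the TIS and the FAC".
- **Who allocates (Allocation).** "A blinded investigator will allocate patients to the control or the experimental group by means of concealed envelopes", with the envelopes stored off site.
- **Who knows (Blinding).** "Only the primary investigator will have knowledge regarding allocation". The section does not say when that knowledge is acquired.
- **Envelope type (abstract, Methods and design).** Allocation is "by means of sealed opaque envelopes".

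Under Exclusion criteria, a TIS score of 20 or more, or a FAC score below 2, excludes a patient. Both are scored by a rater.

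**The concern.** Concealment requires that whoever decides on a patient's entry cannot know or predict the arm. Here the last entry decision belongs to the one person the article names as knowing allocation. The allocations come from a pool of known composition, so anyone who has seen the earlier ones can work out what is left. Nothing in the text requires the decision to be made and recorded before the envelope is drawn.

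At stake is selection bias in the Tinetti Test (TT) comparison. A patient near a cut-off could be scored in or out with a view on the likely arm. This matters more because the article accepts that patients and therapists are unlikely to stay blind, so concealment at entry is one of the main protections left. Adjustment for recorded baseline TIS or FAC could remove part of such a bias, but not selection on unrecorded impressions of prognosis.

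Separately, the randomization method is misnamed, and the sections do not agree on who allocates and who knows.

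**Working it through.** **1. Is the scheme simple randomization?** Inputs: 60 envelopes, 30 per group, used up one by one. Under simple randomization each patient has an independent 50% chance of either arm, and an exact 30/30 split has probability C(60,30)/2^60 = 1/9.749 = 0.103. The envelope pool forces 30/30 with certainty. It is a random allocation rule (all 30/30 sequences equally likely), not simple randomization.

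**2. How predictable is it to someone who knows past allocations?** Assumptions: all earlier allocations are known, all 60 envelopes are used, and the guess is always the arm with more envelopes left. For n per arm,

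expected correct guesses = n + (4^n / C(2n,n) − 1)/2.

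With n = 30: 30 + (9.749 − 1)/2 = 30 + 4.37 = 34.4 of 60, or 57.3%. Without that knowledge the figure is 30 of 60 (50%).

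The patient-by-patient hypergeometric calculation gives the same total:

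| Patient | Chance of a correct guess |
|---|---|
| 20 | 53.6% |
| 30 | 55.1% |
| 40 | 57.2% |
| 45 | 58.4% |
| 47 | 59.2% |
| 50 | 61.2% |
| 55 | 64.8% |
| 58 and 59 | 74.6% |
| 60 | 100% |

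The mean over the last ten is 70.2%. The expected number of fully determined allocations is 2 × 30/31 = 1.9.

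**3. How much of this lies ahead?** Current study status reports 28 patients recruited. Over patients 29 to 60 the expected correct guesses are 19.6 of 32 (61%). That is an excess of 19.6 − 16 = 3.6, out of 4.4 for the whole trial.

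**4. What could it do to the estimate?** Suppose every enrolled patient's prognosis is shifted by +h or −h TT points according to the guess. The documents give no h, so it is an assumption. The bias is h × (34.37 − 25.63)/30 = 0.29h: 0.3, 0.6 or 0.9 points for h = 1, 2 or 3. The planning difference under Sample size is 13.45 − 5.2 = 8.25 points, so h = 2 gives about 7% of it. This is a ceiling for that h, because it lets the screener act on every patient.

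**5. Do the sections agree?**

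| Section | Who allocates | Who knows |
|---|---|---|
| Study design and setting | Independent researcher draws and assigns | That researcher, necessarily |
| Allocation | An investigator described as blinded | By that description, not the allocator |
| Blinding | Not stated | The primary investigator alone |

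Whoever opens an envelope and assigns the patient learns the arm, so the first and third rows cannot both be literally true.

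**The case against.** The stated safeguards are substantial. The envelopes are sealed and opaque, kept off site, and drawn by someone outside assessment and treatment, so the next allocation is hidden from the screener. That stands. It limits the weakness to prediction from running counts, which is modest for most of the trial.

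A reader might infer that the draw comes before screening, so that the screener knows every patient's arm and the bias reaches 2h (4 points at h = 2). The wording allows that order, but the documents do not support treating it as the plan. Recruitment and selection presents TIS/FAC screening as the last of three consecutive steps. The Procedures then run from selection to baseline assessment to allocation. Sixty envelopes for a required 60 patients also leave none to spend on screening failures. The schedule figure, not available here, may settle the order.

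It can also be argued that the Blinding sentence concerns who holds the key to the patient codes, since it follows a sentence on coded data. That is possible. When the primary investigator learns each allocation is not written, so knowledge of past allocations during screening is an inference.

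Finally, room for manoeuvre is confined largely to borderline scores, treating physiotherapists identify candidates first, and the article reports an ICC of 0.96 for the TIS. These points reduce the likely bias. They do not remove the structural problem or the contradictions.

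**Conclusion.** The point holds in this form: concealment is not secured as written. To say that it fails would go further than the text, given the envelope safeguards and the more natural reading that screening comes first.

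On that reading, and if the primary investigator knows past allocations while screening, predictability averages 57% and is concentrated at the end: about 70% over the last ten patients and certainty for about two. Full knowledge of every arm needs the less likely order, so the 4-point figure is a worst case on an assumed h and not an estimate.

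Two errors do not depend on any of these assumptions: the scheme is misnamed, and the sections conflict on who allocates and who knows. This is more than missing detail, because the text gives one person two roles that should be kept apart.

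**What to change.** 1. State the order: consent, TIS/FAC eligibility and the full baseline assessment are completed and recorded before the independent researcher opens an envelope.
2. Keep allocations from the primary investigator while recruitment is open, or have eligibility confirmed by existing staff without access to them. Either brings the screener's chance of guessing the next arm back to 50%.
3. Name one allocator, and say who learns each allocation and when.
4. Replace the term simple randomization with the scheme in use: a random allocation rule with 30 per arm.
5. Make Study design and setting, Recruitment and selection, Allocation and Blinding agree.

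Permuted blocks are not part of the remedy. For someone who knows the running counts, the same formula gives 70.8%, 68.3% and 66.6% correct guesses for blocks of 4, 6 and 8, against 57.3% for the present pool.

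The cost is protocol wording and a change in who sees the allocations. No extra patients or staff are needed, and the envelopes can stay as they are. With 28 patients reported as recruited, the change would still cover most of the predictability.

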### Participants

#### Inclusion criteria

Patients will have to meet the following eligibility criteria to be included in the study: (1) a hemorrhagic or ischemic stroke diagnosis, confirmed on the basis of computed tomography (CT) imaging or magnetic resonance imaging (MRI), (2) no known history of previous stroke, (3) stroke onset within the previous 5 months, and (4) patients are between 18 and 85 years of age.

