#### Exclusion criteria

Patients will be excluded from the study if: (1) they scored 20 or higher on the TIS which indicates normal truncal function [14]. Since patients should be able to improve their trunk performance by means of trunk rehabilitation, normal trunk performance should be excluded [14], (2) they scored lower than 2 on the Functional Ambulation Categories (FAC) as patients need to be able to ambulate without physical support to ensure that gait analysis can be executed safely, (3) they are not able to sit independently, without support and supervision, for 30 s on a stable surface. Patients will have to perform trunk exercises on unstable surfaces; therefore, a minimum truncal function is necessary to ensure a safe environment during training, (4) they suffer from other neurological and orthopedic disorders that could influence motor performance and balance, (5) they are unable to understand verbal instructions. The cognitive and communicative abilities of the patients will be assessed by a neuropsychologist or speech therapist of the rehabilitation hospital RevArte, and (6) they are patients over the age of 85 years because an hour of intense therapy will be too demanding for this population. Additionally, unpublished data from our research group suggest that involvement of the trunk during walking clearly changes after the age of 80 years. This decision was made to exclude gait patterns that resemble a geriatric gait pattern instead of a hemiplegic pattern. Although the patient population needed for this study is specific to patients who are able to walk and have an impaired truncal function, based on unpublished data, it is anticipated that approximately 35% of all hospitalized stroke patients will meet these criteria.

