### Outcome measures

#### Primary outcome measures

Gait performance as measured clinically via the TT is the primary outcome measure. The FAC will not be used as an outcome measure to assess gait performance as it is a more descriptive clinical measure and less detailed compared to the TT. The TT measures gait and balance using a 2- or 3-point ordinal scale with scores ranging from 0 to 1 or 2. The maximum score of the total TT is 28 points, whereby a maximum of 12 and 16 points can be obtained for gait and balance subscales, respectively. Nine items, such as sit to stand, standing balance with eyes open and eyes closed, turning 360° and sitting down, are assessed on the balance subscale. The gait subscales assess eight items ranging from step length, step symmetry, foot clearance, and step width. Reliability and validity of the TT for stroke patients have been reported (ICC2,1 = 0.84; TT-FIMmotor *r* = 0.55; TT-gait speed *r* = 0.82) [39]. The minimal clinically important difference of the TT is 7 points (area under the curve (AUC) = 0.743) and a minimal detectable change of 6 points [39].

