### Statistical analysis

Descriptive data analysis will be performed for the collected variables of the participants. The Kolmogorov-Smirnov Test and visual inspection of the data will be performed to evaluate whether the data are normally distributed. Differences between the experimental and control groups for the clinical data will be evaluated by means of repeated measures (ANOVA). Level of significance will be set at *p* < 0.05. When the stroke population is too heterogeneous, stratified sampling will be done to divide the study population into more homogenous groups. Differences along the entire kinematic, kinetics, and EMG curves will be assessed by means of spm1d in MATLAB®. Statistical parametric mapping will make interference about the topological features of statistical processes that are continuous functions [44].

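### Time since stroke ranges up to 5 months at entry and is already recorded, but neither the allocation nor the stated clinical analysis uses it, which costs some precision and leaves room for chance imbalance

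*Protocol article*

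**What the plan says.** - **Entry window.** Under Inclusion criteria, the timing condition is "stroke onset within the previous 5 months". There is an upper bound only. Exclusion criteria add functional floors: patients below category 2 on the Functional Ambulation Categories (FAC), or unable to sit unsupported for 30 s, are not eligible.
- **Allocation.** Under Study design and setting, patients are "randomly allocated to either the experimental or the control group by simple randomization", drawn from one pool of 60 envelopes, 30 per arm. No stratification factor is named.
- **Data in hand.** Recruitment and selection states: "Information concerning stroke diagnosis, medical history, and stroke onset will be acquired from patient records". Apart from eligibility, no described step uses the onset date.
- **Outcome and analysis.** "Gait performance as measured clinically via the TT is the primary outcome measure". For the clinical outcomes, Statistical analysis names a repeated measures ANOVA comparing the two groups and mentions no covariate.
- **Heterogeneity.** The same section adds that stratified sampling will divide the population into more uniform groups if it proves too heterogeneous. It does not say heterogeneous in what, by how much, or whether the division happens at recruitment, allocation or analysis.

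**The concern.** The primary question concerns change in the Tinetti Test over 4 weeks. A window open up to 5 months can pool patients a few weeks after stroke with patients several months after it, and their background recovery over those 4 weeks may differ. The article gives no figure for this. It does show that background change is not negligible: the control arm of the earlier trial cited under Sample size gained 5.2 points, close to the minimal detectable change of 6 points given under Primary outcome measures. That gain mixes usual care with natural recovery.

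A repeated measures ANOVA removes stable differences in level between patients. It does not remove differences in rate of recovery, which stay in the error term of the group-by-time contrast. Two patients with the same baseline Tinetti score at different times after stroke may be on different courses, so the baseline score does not fully stand in for time since onset.

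Two things are at stake: a wider error than necessary for the primary comparison, and a chance excess of early patients in one arm that the stated analysis would not correct.

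**Working it through.** **1. The plan's own figure.** Sample size gives change scores of 13.45 and 5.2 (difference 8.25), 30 per group, 80% power and two-sided 5%, but no SD. The 30 per group therefore cannot be reproduced. Solving for the SD:

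SD = 8.25 × √15 / (1.960 + 0.842) ≈ 11.4 (11.2 with the t distribution).

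This is an assumption used below, not a figure from the article. The standard error of the group difference is then 11.4 × √(2/30) ≈ 2.9 points.

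**2. Chance imbalance, early versus late.** Assume 30 of the 60 patients are early. With 30 envelopes per arm, the number of early patients in one arm is hypergeometric (60, 30, 30):

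- arms differ by 6 or more (18:12 or worse): 19.6%
- arms differ by 8 or more: 7.0%

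Each total divides equally between excesses favouring either arm.

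**3. Shift at an 18:12 split.** Shift = (18 − 12)/30 × extra gain of early patients = 0.2 × extra gain. For assumed extra gains of 3, 5 and 8 points the shift is 0.6, 1.0 and 1.6 points, or about 0.2 to 0.5 standard errors.

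**4. The same question with time as continuous.** Assume entry times uniform on 0 to 5 months, so SD = 5/√12 = 1.44 months. The between-arm difference in mean time has standard error 1.44 × √(2/30) = 0.37 months. Its 95% range is ±0.73 months, and it exceeds half a month in 18% of allocations. At the 95% limit the Tinetti contrast shifts by r × 11.4 × 1.96 × √(2/30), where r is the correlation of time since onset with Tinetti change: 1.2 points at r = 0.2, 1.7 at r = 0.3 and 2.9 at r = 0.5.

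**5. Precision gained by adjusting.** Residual SD = 11.4 × √(1 − r²), with difference 8.25 and 30 per group:

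| r (assumed) | Power | n per group for 80% |
|---|---|---|
| 0 | 80% | 30 |
| 0.2 | 81.6% | 29 |
| 0.3 | 83.6% | 28 |
| 0.4 | 86.4% | 26 |
| 0.5 | 89.9% | 23 |

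**6. Do the assumptions agree?** With half the patients early, r = 0.5 × extra gain / SD. At SD 11.4, gains of 3, 5 and 8 points give r ≈ 0.13, 0.22 and 0.35. The effective sample size, 60/(1 − r²), is then about 61, 63 and 68. Reaching r = 0.5 at that SD would need an extra gain of 2 × 0.5 × 11.4 = 11.4 points, more than the planned treatment effect. A smaller SD would raise r for the same gain, but the planned power would then already be well above 80% (97.9% at SD 8).

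**The case against.** The strongest objection is that covariates are normally left to the analysis plan, which is not shown, and that a wide window with unstratified allocation is a legitimate choice for 60 patients at one site. Much of this stands: nothing here is contradictory, and an analysis plan may already list covariates. It does not settle the matter, because the article itself fixes the unstratified draw, names the analysis without this term and states its own heterogeneity rule. That rule cannot do the work. Sampling cannot be stratified once patients are enrolled, and dividing 60 patients after seeing that they vary would be a post hoc split.

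Second, the FAC and sitting criteria, together with the rehabilitation-hospital setting, probably keep out very early patients, so the real spread may be narrower than 0 to 5 months. That is fair and makes the uniform assumption in step 4 generous. The criteria do not stop patients weeks and months after stroke from being pooled.

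Third, no passage quantifies how Tinetti change depends on time since onset. That stands in full: every size above is conditional on an assumption.

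A reader might infer that the primary comparison is biased or its test invalid. The documents do not support that. Randomization makes the contrast unbiased on average, and chance imbalance is already reflected in the standard error and the significance level. A reader might also expect adjustment to be worth many more patients. At the back-solved SD, gains of 3 to 8 points support about 61 to 68 effective patients instead of 60.

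**Conclusion.** The point holds as an inexpensive improvement to the analysis, not as an error that undermines the trial. Time since onset is collected, may be prognostic for the primary change score, and is used neither in allocation nor in the stated clinical analysis; the heterogeneity sentence does not fill the gap.

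The size is modest. A notable early/late imbalance occurs in about one allocation in five if half the patients are early, and an 18:12 split then moves the contrast by 0.6 to 1.6 points against a planned 8.25. Adjustment adds about 2 to 4 percentage points of power at r = 0.2 to 0.3, and about 10 at r = 0.5. These figures rest on the SD of about 11.4 back-solved from the stated sample size, on the assumed share of early patients and their extra gain, and on a correlation that the article does not give.

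**What to change.** Prespecify time from stroke onset to baseline, on a scale chosen in advance, as a covariate in the analyses of the Tinetti Test, the Trunk Impairment Scale and the Barthel Index. Either form works:

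- a model at each post-treatment visit adjusted for the baseline score and time since onset, where the new term costs one degree of freedom; or
- the repeated-measures model with time since onset and its interaction with visit. A main effect alone is not enough: it is constant within a patient, cancels from the change over time and leaves the group-by-time contrast as it was.

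Let this replace the undefined heterogeneity sentence, and show time since onset by arm in the baseline table.

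The cost is analysis wording, settled before outcomes are examined by arm. The onset date is already obtained at screening. Current study status reports 28 patients recruited, so the change belongs in the analysis: envelopes, patients and data collection stay as they are.
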